### 3.2 Secondary Endpoint:

- 1) The proportion of lupus low disease activity state (LLDAS) at week 96.
- 2) Short form-36 (SF-36) score of before and after treatment in two groups.
- 3) The proportion of adverse events of two groups in the follow-ups.
- 4) Changes in SLEDAI-2000 score.
- 5) Changes in prednisone dose.

## 4. Study design

In this study, we randomly assigned patients (1:1) to Control group and MMF group. Control group received treatment with HCQ (5mg/kg/day) and prednisone (0.5mg/kg/day); while MMF group received treatment with HCQ (5mg/kg/day) and prednisone (0.5mg/kg/day) plus MMF 500mg twice daily. The dose of MMF stayed the same unless a contrary or severe adverse event occurred.

Prednisone dose was tapered as follows:

Initial dose (0.5mg/kg/day) maintained for four weeks

[figure not shown]

tapered 5mg every two weeks till to 20 mg/day

↓

tapered 5mg every month

↓

gradually to 0.1-0.2mg/kg/day

The taper of prednisone doses was determined by the physicians according to the assessment of patients.

Notes:

- 1) Patients with severe flare were not involved in subsequent treatment plan, but they were still being followed up consistently until the end of the entire process.
- 2) Patients who met the criteria of severe flare were treated with increased doses of prednisone (more than 0.5mg/kg/day), immunosuppressive therapy or hospitalized for treatment according to the patients' condition and the physician's assessment.
- 3) Patients with mild to moderate flares continued to be followed up till the end of Week 96, and all flare episodes were recorded.
- 4) Patients with mild to moderate flares could increase the dose of prednisone (less than 0.5mg/kg/day) or nonsteroidal anti-inflammatory drugs.
- 5) For fever, rash, and arthritis, the dose of prednisone could be used at an initial dose of less than 0.5mg/kg/day, and following the assessment of symptoms, the dose could be increased to more than 0.5mg/kg/day if needed.
- 6) Any sign of kidney involvement (glomerular haematuria and/or cellular casts, proteinuria >0.5g/24hours (or spot urine protein-to-creatinine ratio (UPCR) >500mg/g), unexplained decrease in glomerular filtration rate (GFR)), renal biopsy was suggested to confirm the diagnose of LN. Results of renal biopsy were confirmed by a senior nephrologist ([name]). The treatment of LN was provided according to the European Renal Association-European Dialysis and Transplant Association (ERA-EDTA) guideline.
- 7) The treatment of other organ involvement was provided following the 2019 European League Against Rheumatism (EULAR) recommendation.

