## **6.5 Methods of subject assignment**

Participants were randomly assigned (1:1) using blocks of four to receive either MMF (MMF group) or a control treatment (Control group). A statistician from the Clinical Trial Center of Ruijin Hospital, [name], who was masked to trial allocation generated the randomization sequences by a computer algorithm. Then, random numbers were written on the cards and packed in sequentially numbered envelopes that were opened when the patients were enrolled. [name] assigned patients to different groups according to the number on the card. Only Assessors were masked to the group allocation. Eligible subjects were recruited from the Department of Rheumatology and Immunology of Ruijin Hospital and the Department of Rheumatology and Immunology of the other two clinical centers.

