### **3. Study outcomes**

#### **3.1 Primary Endpoint:**

The primary outcome was the proportion of patients who have flares (mild to moderate flares and severe flares) defined by modified SELENA-SLEDAI Flare Index (SFI)  at 96 weeks of follow-up.

The definition of mild to moderate flare is the fulfillment of one or more following items:

- 1) variation of SELENA-SLEDAI score  $\geq 3$  (but  $< 12$ );
- 2) new or worsening rashes, cutaneous vasculitis, nasopharyngeal ulcers, serositis, arthritis or fever caused by lupus;
- 3) increase in the dose of prednisone, but less than 0.5mg/kg/day;
- 4) increase of nonsteroidal anti-inflammatory drugs or HCQ;
- 5) Physician's Global Assessment (PGA) (0-3 scale)  $\geq 1$ .

Severe flare is defined as the fulfillment of one or more of the following items:

- 1) change in SELENA-SLEDAI score of more than 12;

- 2) new or worsening central nervous system involvement, vasculitis, nephritis, myositis, thrombocytopenia (platelet  $<60 \times 10^9/L$ ) or haemolytic anaemia (haemoglobin  $<70g/L$  or decrease in haemoglobin level  $>30g/L$ );
- 3) increased usage of prednisone (doubled in dosage or more than 0.5mg/kg/day);
- 4) added cyclophosphamide, azathioprine, methotrexate, mycophenolate mofetil or hospitalization because of lupus activity;
- 5) PGA  $>2.5$ .

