## **6. Sample size calculation**

We referred to the flare rate of the placebo arm in 'Met Lupus' trial and the flare rate from the BLISS-52, BLISS-76 and BLISS-North East Asia phase III trials. We supposed the flare rate to be 10% in MMF group and 30% in Control group. Z test with unpooled variance ( $\alpha=0.0568$ ,  $\beta=0.1964$ ,  $\text{power}=0.8036$ ) was used for

sample size calculation. A sample size of 58 patients per group would provide the trial with 80% power at a two-sided alpha error of 0.05 to detect a difference between the two groups using the software PASS version 11.0. Taking an estimated 10% drop-out into account, a sample size of 65 patients per group could fulfill the statistical requirement. The sample size was calculated using PASS version 11.0 software as follows:

| Two Independent Proportions (Null Case) Power Analysis                      |                         |                         |                                     |                                   |                     |                     |                 |                 |        |
|-----------------------------------------------------------------------------|-------------------------|-------------------------|-------------------------------------|-----------------------------------|---------------------|---------------------|-----------------|-----------------|--------|
| Numeric Results of Tests Based on the Difference: P1 - P2                   |                         |                         |                                     |                                   |                     |                     |                 |                 |        |
| H0: P1-P2=0. H1: P1-P2=D1<>0. Test Statistic: Z test with unpooled variance |                         |                         |                                     |                                   |                     |                     |                 |                 |        |
|                                                                             | Sample
Size
Grp 1 | Sample
Size
Grp 2 | Prop H1
Grp 1 or
Trtmnt
P1 | Prop
Grp 2 or
Control
P2 | Diff
if H0
D0 | Diff
if H1
D1 | Target
Alpha | Actual
Alpha | Beta   |

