### **8.5 Primary outcome**

Flare proportion was defined as categorical variables, data were expressed in the form of frequency (percentages). The primary outcome was the proportion of patients with flares (including mild-to-moderate flares and severe flares) during follow-up. Safety of Estrogens in Lupus Erythematosus National Assessment-Systemic Lupus Erythematosus Disease Activity Index (SELENA-SLEDAI) Flare Index (SFI) was used for assessing disease flares in this trial. Pearson Chi-square or Fisher's exact tests were used to compare between-group differences. We first calculated the total flare rate, and then calculated mild-to-moderate flare rate and severe flare rate, respectively.

For the primary outcome, Bonferroni correction was used and two-sided at a significance level of 0.025. A more stringent statistical criterion was used. Relative risk (RR) was employed to compare the proportion of patients with the end point between MMF group and Control group. Severe flare-free survival proportion was estimated by using the Kaplan-Meier method in the intention to MMF group and Control group with a log rank test. Regarding patients who dropped out of the study, we collected all of the data during follow-up period. For patient who loss to follow-up, we did not collect the data for the subsequent time after lost to follow-up event. We used the ITT set for primary outcome calculation. All of the patients were included in the denominator. We estimated the severe flare-free survival proportion of the MMF group and Control group in both ITT and PP Set using the Kaplan-Meier method.

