**Table 3 Outcomes of 96-week follow-ups.**

|  | Control group | MMF group | RR | P value |
|--|---------------|-----------|----|----------------|
|  |               |           |    |                |

|                                            | (n=)                  | (n=)                  |          |
|--------------------------------------------|-----------------------|-----------------------|----------|
|                                            | Mean (SD) or
N (%) | Mean (SD) or
N (%) | (95% CI) |
| Primary outcome, %                  |                       |                       |          |
| Proportion of severe flares                |                       |                       |          |
| Proportion of mild to moderate flares      |                       |                       |          |
| Severe flares, %                    |                       |                       |          |
| Lupus nephritis                            |                       |                       |          |
| Neuropsychiatric symptoms                  |                       |                       |          |
| Rash (prednisone dose > 0.5mg/kg/day)      |                       |                       |          |
| Pleurisy                                   |                       |                       |          |
| Thrombocytopenia (<60* 10  /L) |                       |                       |          |
| Pulmonary arterial hypertension            |                       |                       |          |
| Hemolytic anemia                           |                       |                       |          |
| Fever (prednisone dose > 0.5mg/kg/day)     |                       |                       |          |
| Henoch-Schonlein purpura                   |                       |                       |          |
| Moderate mitral insufficiency              |                       |                       |          |
| Arthritis (prednisone dose > 0.5mg/kg/day) |                       |                       |          |

**Mild to moderate flares,  
%**

Arthritis

Rash

Oral ulcer

Fever

Leukopenia  
( $1.5-4 \times 10^9/L$ )

Thrombocytopenia  
( $60-100 \times 10^9/L$ )

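### For rash, fever and arthritis, Table 3 separates severe from mild-to-moderate flare only by a prednisone dose chosen by an unmasked physician, so the severity split and the severe flare-free curve can differ between arms with equal disease

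*Combined protocol and SAP*

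**What the plan says.** - **Dose rule.** SAP section 4, note 5, and protocol 8.1(5) cover fever, rash and arthritis. Prednisone starts below 0.5 mg/kg/day and, following assessment of symptoms, "the dose could be increased to more than 0.5mg/kg/day if needed". No numerical trigger is given.
- **Flare definition.** SAP 3.1 lists new or worsening rash, arthritis or fever as mild-to-moderate, along with a prednisone increase below 0.5 mg/kg/day. Severe item 3 is "increased usage of prednisone (doubled in dosage or more than 0.5mg/kg/day", and meeting one item is enough. The other severe items are a SELENA-SLEDAI change above 12 (item 1), listed organ or haematological events (item 2), an added immunosuppressant or hospitalization (item 4) and PGA above 2.5 (item 5).
- **Output shell.** SAP Table 3 has rash, fever and arthritis in both blocks. The severe rows carry only a dose label, for example "Rash (prednisone dose > 0.5mg/kg/day".
- **Masking.** Protocol 6.5 says "Only Assessors were masked to the group allocation". Protocol 7.3 adds observers and data analysts. Placebo is ticked as not used in the brief list, and protocol 7.2.1 has patients buy the drugs on prescription from the outpatient pharmacy.
- **Analysis.** SAP 8.5 computes the total flare rate first, then the two levels. SAP 8.2 sets 0.025 for the two levels. Severe flare is also the time-to-event outcome: "Severe flare-free survival proportion was estimated by using the Kaplan-Meier method".

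**The concern.** A masked assessor who applies the index perfectly still records a dose that someone else chose knowing the arm. SAP 8.1 relies on flare being assessed strictly by the index and not by subjective decisions, but the index as written takes in a prescribing decision.

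If physicians cross the 0.5 mg/kg/day line more readily in one arm for the same rash, fever or arthritis, flares move between the severe and mild-to-moderate levels in that arm only. A severe-flare difference could then reflect prescribing and not disease. No planned analysis separates the two: the per-protocol Kaplan-Meier analysis in SAP 8.5 uses the same event definition.

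**Working it through.** **The plan's own figure.** SAP section 6 states: "We supposed the flare rate to be 10% in MMF group and 30% in Control group", with "80% power at a two-sided alpha error of 0.05" and "Test Statistic: Z test with unpooled variance". Exact binomial enumeration of that test at 58 per group gives power 0.8036 and actual alpha 0.0568 (at 30% in both groups), as printed. Dropout: 58 / 0.90 = 64.4, so 65. The sample size reproduces and is not in dispute.

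**Inputs from the documents.** 65 per arm (SAP 6); 0.025 two-sided (SAP 8.2, 8.5); Pearson chi-square (SAP 8.5).

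**Assumed inputs.** Disease is identical in both arms. Each patient is counted at one level, the highest reached. s = 5% per arm have a severe flare by another route. m = 10% or 20% per arm have a rash, fever or arthritis flare that is severe only if the dose is raised above 0.5 mg/kg/day. e is the probability that the dose is raised, and it may differ by arm. The documents give none of s, m or e, and no direction. More escalation in control is taken for illustration.

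**Formulas, per arm.**
- Severe = s + m × e
- Mild-to-moderate = m × (1 − e)
- Total = s + m, which does not contain e

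Example, m = 20%, e = 60% in control and 20% in MMF:
- Severe: 5% + 20% × 0.60 = 17% against 5% + 20% × 0.20 = 9%.
- Mild-to-moderate: 20% × 0.40 = 8% against 20% × 0.80 = 16%.
- Total: 25% in both arms.

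The rejection probability is the sum of the binomial probabilities of all outcome pairs that the chi-square test rejects at 0.025, in either direction.

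| m | e, control vs MMF | Severe, control vs MMF | Chance of p < 0.025 for severe flare | Total, both arms |
|---|---|---|---|---|
| 20% | 50% vs 50% | 15% vs 15% | 2.4% | 25% |
| 20% | 50% vs 40% | 15% vs 13% | 3.1% | 25% |
| 10% | 50% vs 25% | 10% vs 7.5% | 3.9% | 15% |
| 10% | 60% vs 20% | 11% vs 7% | 6.7% | 15% |
| 20% | 50% vs 25% | 15% vs 10% | 8.0% | 25% |
| 20% | 60% vs 20% | 17% vs 9% | 18.1% | 25% |

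All totals stay below the plan's 30% control rate. The mild-to-moderate comparison moves the other way: in the last row its own rejection probability is 19.4%, against MMF. The log-rank test was not simulated. It uses the same severe events, so it is open to the same shift.

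**The case against.** Five points on the other side carry weight.

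1. A reader might infer that dose is the only thing that ever separates the two levels for these symptoms. That is true of the Table 3 rows. It is not true of SAP 3.1, where such a flare can also become severe through the SELENA-SLEDAI change, an added immunosuppressant, hospitalization or PGA.
2. A reader might infer that the primary result as a whole is biased. The documents do not support that. The endpoint is any flare, SAP 8.5 computes the total first, and the sample size rests on a single flare rate. Moving an event between levels leaves the total unchanged.
3. Escalation is tied to an assessment of symptoms, so it is not arbitrary, and protocol 7.3 gives follow-up assessments to masked observers. This helps only in part. No threshold is stated, the prescriber still knows the arm, and SAP 8.1 gives follow-up assessments to the doctors who include patients.
4. Planned output would show part of the problem. Table 3 lists the three dose-labelled rows by arm, and the mild-to-moderate comparison would move in the opposite direction. What is missing is a re-test and a Kaplan-Meier version.
5. The size rests on assumed inputs. A 10-point gap in escalation barely moves the error rate (3.1%), and nothing in the documents shows that control patients would get the higher doses. This stands, so the figures are a range and not an estimate.

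**Conclusion.** The point holds for the severity split and the severe flare-free comparison, and not for the total flare proportion. A dose decision by a physician whom no passage masks is sufficient for a severe flare, so those analyses can show a difference with equal disease. Under the assumptions above, the false-positive chance for severe flare lies between about 3% and 18%, against 2.4% with equal escalation. The documents cannot show that such a difference occurred, or which arm it would favour, so it should not be read as evidence of bias in the results. It is a limit on interpreting any severe-flare claim, and an inexpensive sensitivity analysis would address most of it.

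**What to change.** **SAP 8.5.** Pre-specify a sensitivity analysis of the severe-flare proportion and of the Kaplan-Meier and log-rank comparison in which severe flare requires item 1, 2 or 5 of SAP 3.1. Events severe only through a treatment decision (item 3, including a doubled dose, or item 4) are counted as mild-to-moderate. Item 4 has to go with item 3: an added drug or a hospitalization is also a treatment decision, and SAP section 4, note 2, allows either after a severe flare has been declared.

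**Derivation.** Use the flare-index items met at each flare, recorded with the first-met item and its date. The Table 3 rows will not do: they omit the doubled-dose route, and pleurisy is a severe row with no dose label although serositis is a mild-to-moderate item.

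**Reporting.** Show the result beside the main severe-flare result and state whether any difference survives. The total flare proportion is unchanged.

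**Reconcile.** Protocol 7.3 and SAP 8.1 differ on who does the follow-up assessments and should be brought into line.

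**Cost.** One SAP paragraph, an extra row in Table 3, and recording of the item met. The analysis will have fewer severe events and a wider interval. PGA (item 5) still involves judgment, so discretion is reduced and not removed. No dose or treatment rule is changed or proposed.

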## **5. Participant selection**

During enrolment, patients were required:

### **5.1 Inclusion Criteria:**

- 5) Age between 18 and 65 years old;
- 6) Diagnosed with SLE at the time of screening by fulfilling ACR 2019 classified criteria or its 2017 version;
- 3) Have not received any prior SLE treatment;
- 4) Have a positive antinuclear antibody (HEp-2 titer  $\geq 1:80$ );
- 5) Have a positive anti-dsDNA antibody (fulfilled both anti-dsDNA (ELISA)  $\geq 300$  IU/mL and anti-dsDNA (CLFT)  $\geq 1:10$ );
- 6) Do not have major organ involvement (i.e., brain, heart, liver, kidney, lung, muscle, serous cavity and gastrointestinal tract). Participants were permitted to have rash, arthritis, alopecia, oral ulcer, and mild hematologic system involvement (white blood cell  $>1.5 \times 10^9/L$  and  $<4 \times 10^9/L$ , hemoglobin  $>90g/L$  and  $<120g/L$ , platelet  $>60 \times 10^9/L$  and  $<100 \times 10^9/L$ ).

### **5.2 Exclusion Criteria:**

- 1) SLE patients who had been treated;
- 2) Liver and kidney dysfunction (Alanine aminotransferase (ALT)/ aspartate aminotransferase (AST)  $> 2$  times upper normal limits; creatinine clearance rate  $< 60ml/min$ );
- 3) Cancer;
- 4) Recent infection or hematologic diseases not caused by SLE;
- 5) Pregnancy or planned to be pregnant;
- 6) Patients not willing to join the study.

## **6. Sample size calculation**

We referred to the flare rate of the placebo arm in 'Met Lupus' trial and the flare rate from the BLISS-52, BLISS-76 and BLISS-North East Asia phase III trials. We supposed the flare rate to be 10% in MMF group and 30% in Control group. Z test with unpooled variance ( $\alpha=0.0568$ ,  $\beta=0.1964$ ,  $\text{power}=0.8036$ ) was used for

sample size calculation. A sample size of 58 patients per group would provide the trial with 80% power at a two-sided alpha error of 0.05 to detect a difference between the two groups using the software PASS version 11.0. Taking an estimated 10% drop-out into account, a sample size of 65 patients per group could fulfill the statistical requirement. The sample size was calculated using PASS version 11.0 software as follows:

| Two Independent Proportions (Null Case) Power Analysis                      |                         |                         |                                     |                                   |                     |                     |                 |                 |        |
|-----------------------------------------------------------------------------|-------------------------|-------------------------|-------------------------------------|-----------------------------------|---------------------|---------------------|-----------------|-----------------|--------|
| Numeric Results of Tests Based on the Difference: P1 - P2                   |                         |                         |                                     |                                   |                     |                     |                 |                 |        |
| H0: P1-P2=0. H1: P1-P2=D1<>0. Test Statistic: Z test with unpooled variance |                         |                         |                                     |                                   |                     |                     |                 |                 |        |
|                                                                             | Sample
Size
Grp 1 | Sample
Size
Grp 2 | Prop H1
Grp 1 or
Trtmnt
P1 | Prop
Grp 2 or
Control
P2 | Diff
if H0
D0 | Diff
if H1
D1 | Target
Alpha | Actual
Alpha | Beta   |
| Power                                                                       | N1                      | N2                      |                                     |                                   |                     |                     |                 |                 |        |
| 0.8036                                                                      | 58                      | 58                      | 0.1000                              | 0.3000                            | 0.0000              | -0.2000             | 0.0500          | 0.0568          | 0.1964 |

Reference:

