## **8. Statistical procedures**

### **8.1 Randomization and masking**

Participants were randomly assigned (1:1) using blocks of four to receive either MMF (MMF group) or a control treatment (Control group). A statistician from the Clinical Trial Center of Ruijin Hospital, [name], who was masked to trial allocation generated the randomization sequences by a computer algorithm. Then, numbers were written on the cards and packed in sequentially numbered envelopes that were opened when the patients were enrolled. [name] assigned patients to different groups according to the number on the card. Assessors were masked to the group allocation. Eligible subjects were recruited from the Department of Rheumatology and Immunology of Ruijin Hospital and the Department of Rheumatology and Immunology of the other two clinical centers. Doctors were responsible for patient inclusion and regular follow-up assessments ([name], [name], [name], [name], and [name]). The assessment of patient flare was strictly based on the SELENA-SLEDAI Flare Index (including severe flare, and mild to moderate flare) rather than subjective decisions. Data analysts ([name] and [name]) were not involved in patient assessment and treatment, and they were masked to the group allocation.

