### **8.2 Analysis principles**

- 1) For the primary outcome assessed at two levels (mild-to-moderate and severe flares), Bonferroni correction was used and two-sided at a significance level of 0.025. Other tests were performed two-sided at the significance level of 0.05. The confidence level for all confidence intervals (CI) will be 95%.
- 2) The number of observations used in the analysis will be reported.
- 3) The statistical analysis plan is drafted prior to database lock, and it includes a detailed description of the statistical analyses. The statistical analyses were performed using SPSS Statistics (version 23.0), GraphPad Prism (version 8.0), and R software

(version 4.0.0). Figures will be plotted using GraphPad Prism (version 8.0) and R software (version 4.0.0).

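### The stated 80% power is calculated at two-sided alpha 0.05, but the primary outcome is tested at 0.025, where the same assumptions give about 70% to 75%.

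*Combined protocol and SAP*

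**What the plan says.** **Sizing.** SAP 6 sets the effect: "We supposed the flare rate to be 10% in MMF group and 30% in Control group". The printed software output names the method, "Test Statistic: Z test with unpooled variance", with target alpha 0.05, actual alpha 0.0568, 58 per group and power 0.8036. The text sums this up as "A sample size of 58 patients per group would provide the trial with 80% power at a two-sided alpha error of 0.05". A 10% drop-out allowance takes 58 to 65 per group. Protocol 5.3 and 6.4 and the protocol summary give the same calculation.

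**Analysis.** SAP 8.5 names the tests, "Pearson Chi-square or Fisher's exact tests were used to compare between-group differences", and the threshold: "For the primary outcome, Bonferroni correction was used and two-sided at a significance level of 0.025". SAP 8.2 gives the reason for the split: "For the primary outcome assessed at two levels (mild-to-moderate and severe flares), Bonferroni correction was used and two-sided at a significance level of 0.025". It then puts all other tests at 0.05. Protocol 10.2 matches SAP 8.2, while protocol 10.1 puts every test at 5%.

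**Denominator and order.** SAP 8.5 uses the ITT set with every patient in the denominator. It calculates the total flare rate first and then each severity level. The Table 3 shell in SAP 15 lists only the two levels under the primary outcome.

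Neither document gives a power or sample size at 0.025, or for the Pearson or Fisher test.

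**The concern.** Power belongs to a particular test at a particular alpha. The 80% here belongs to an unpooled Z test at 0.05, whereas the primary comparison is a Pearson or Fisher test at 0.025. Anyone judging a non-significant primary result would take the type II error to be about 20% at the assumed effect, when under the analysis as written it is larger. The conflict between protocol 10.1 and 10.2 adds to this, because the threshold that decides success is not the same in the two sections.

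**Working it through.** **Inputs, all from the documents.** Rates 0.10 and 0.30 (SAP 6); 58 per group for power and 65 enrolled (SAP 6); 1:1 allocation (SAP 8.1); two-sided alpha 0.05 for sizing (SAP 6) and 0.025 for the primary analysis (SAP 8.2 and 8.5); Pearson or Fisher (SAP 8.5).

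**Method.** List every pair (x, y) of flare counts in the two groups, mark those in which the test rejects, and sum Bin(x; n, 0.10) × Bin(y; n, 0.30) over them. The unpooled Z statistic is |a − b| / √[a(1−a)/n + b(1−b)/n], with a and b the observed proportions. Pearson without correction uses p̄(1−p̄)(2/n) under the root, with p̄ = (a+b)/2. The cut-off is 1.960 at 0.05 and 2.241 at 0.025.

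**Step 1: reproduce the plan.** Unpooled Z, 58 per group, alpha 0.05: power 0.8036, and actual alpha 0.0568 when both rates are 0.30. Both match the printed output. Drop-out: 58/0.9 = 64.4, rounded up to 65, which also matches.

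**Step 2: the planned tests.**

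| n per group | Alpha | Unpooled Z | Pearson | Fisher |
|---|---|---|---|---|
| 58 | 0.05 | 80.4% | 79.7% | 71.6% |
| 58 | 0.025 | 71.0% | 69.9% | 60.7% |
| 65 | 0.025 | 76.2% | 75.4% | 68.6% |

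As a hand check, the usual normal formula with p̄ = 0.20 and 58 per group at 0.025 is Φ[(0.20 − 2.241 × √(0.32/58)) / √(0.30/58)] = Φ[(0.20 − 0.1665)/0.0719] = Φ(0.466) = 67.9%. For 65 per group it is Φ(0.629) = 73.5%. Both lie about two points below the exact values.

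**Step 3: the source of the loss (58 per group).** Changing from unpooled Z to Pearson at 0.05: 80.36 − 79.72 = 0.6 points. Halving alpha with Pearson: 79.72 − 69.85 = 9.9 points.

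**Step 4: drop-out with everyone in the denominator.** Assume that 10% drop out and count as non-flare. The rates become 0.9 × 30% = 27% and 0.9 × 10% = 9%, and Pearson at 0.025 with 65 per group gives 68.8%. The 75.4% in the table applies if all 65 per group count at the full assumed rates.

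**Step 5: Pearson or Fisher.** The SAP has no rule for choosing. At the average rate of 20%, expected flares per arm are 58 × 0.20 = 11.6, above the conventional limit of five, so Pearson is the relevant test for 30% versus 10%.

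**Step 6: power per level, if 30% versus 10% means any flare.** The split between levels is not stated. Keeping the 3:1 ratio as an assumption, with 58 per group and Pearson at 0.025:

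| Assumed rates at one level | Power |
|---|---|
| 6% vs 2% | 9% |
| 15% vs 5% | 31% |
| 24% vs 8% | 57% |

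In the first row the expected count is 58 × 0.04 = 2.3 per arm, where convention would call for Fisher, so 9% is if anything optimistic.

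**The case against.** The best defence is that total flare is not tested at 0.025. SAP 8.2 and protocol 10.2 tie the correction to the two severity levels and leave other tests at 0.05. SAP 8.5 calculates total flare separately from the levels. If total flare counts as one of the other tests and 30% versus 10% describes any flare, Pearson power with 58 per group is 79.7%, practically as stated. This reading is open. However, SAP 8.5 attaches 0.025 to the primary outcome without distinction, just after defining that outcome as flares of both kinds. The reading also leaves the two levels, the only entries under the primary outcome in the Table 3 shell, with no stated power.

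A second defence is that all 65 per group are analysed. That helps, but only to 75.4% at best.

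Some stronger conclusions that a reader might draw are not supported:

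- *The sample size arithmetic is wrong.* It is not; it reproduces to four digits. The fault is a mismatch between sections.
- *Power is about 61%.* That is Fisher with 58 per group. Expected counts would not call for Fisher at the assumed rates, so the Fisher range of 60.7% to 68.6% is only a lower bound.
- *The actual alpha of 0.0568 means that the trial's false-positive rate is inflated.* That figure belongs to the unpooled Z test, which is not the analysis test. Testing at 0.025 is stricter than the sizing assumed, and it changes neither the estimate nor its confidence interval.
- *Each level has about 31% power.* This depends on an equal split that appears nowhere in the documents.

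**Conclusion.** The concern holds as an inconsistency between the sizing and analysis sections. If 0.025 governs the comparison that 30% versus 10% describes, Pearson power is 69.9% with 58 per group and 75.4% with 65 at the full assumed rates. It is 68.8% if 10% drop out and count as non-flare. Type II error is then about 25% to 31%, against the stated 19.6%. If instead 30% versus 10% is any flare and 0.025 governs only the two levels, the 80% stands for total flare, while power for each level is unstated and, on the assumed splits above, runs from 9% to 57%. On no reading do the documents support 80% power for a test at 0.025. Which case applies cannot be settled from the text.

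**What to change.** 1. In protocol 5.3 and 6.4, the protocol summary and SAP 6, replace the unpooled Z output with power for the planned Pearson test at two-sided 0.025: about 70% with 58 evaluable per group, and 75% if all 65 per group count at the assumed rates.
2. State whether 30% versus 10% is any flare, mild-to-moderate flare or severe flare.
3. State which tests 0.025 governs, and in particular whether total flare is one of them.
4. Align protocol 10.1 with 10.2.

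The cost is wording and a less favourable stated power. Correcting the statement needs no extra patients, though it does not bring power back to 80%. Making total flare the single primary test at 0.05 would change the primary hypothesis and relax alpha; that is a separate design decision and not part of this fix.
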